# eAppendix 1: Study protocol

## CheckMyText! Evaluation of the SHeLL Health Literacy Editor

### *Background*

Low health literacy affects more than half (60%) of the Australian population[1] and is associated with higher mortality, morbidity, rates of hospitalisation and emergency department visits, and medication errors.[2] National and international policies recognise health literacy as a critical source of health inequality that disproportionately affects those who are older, less educated, and people from culturally diverse communities (2020 National Health Reform Agreement; WHO Sustainable Development Goals).

A key directive of these policies is to provide health information that all people can easily understand including those with low health literacy. Despite being a relatively simple, low-cost strategy to address health literacy, this directive has not been integrated into routine public health and clinical practice. Research estimates less than 1% of online Australian health information is written simply enough for most people to understand.[3]

The current evidence-base for interventions that produce easy-to-read health information at scale is insufficient. Several health literacy guidelines advise how to structure, write, and visually present health information.[4-6] However, except for school grade reading levels, there are no other tools that objectively assess whether individual words or sentences may be hard to understand. As a result, applying health literacy principles to written text is often time-consuming and highly subjective.

The Sydney Health Literacy Lab (SHeLL) Health Literacy Editor is a new tool developed to address this issue. It provides objective assessment of written health information across a range of factors. These include feedback on school grade reading levels, medical jargon, and complex grammatical structures such as the passive voice. The Editor also guides users in real-time, providing suggested alternatives and demonstrating how small changes can incrementally improve the text. The Editor has undergone extensive user testing with health staff to refine the usability of its features and improve acceptability (manuscript currently under review). However, though the Editor assesses wide-ranging factors that influence text complexity, it is unknown whether health information providers can easily act on this feedback to revise and simplify health information.

### Aim:

This study aims to evaluate whether health information developers produce higher quality written health information (i.e. easier to understand) using the Health Literacy Editor compared to usual processes.

## Part 1: Randomised-controlled trial and process evaluation (health information developers)

### *Methods*

## Study design

This is a two-arm randomised-controlled trial comparing the effect of the intervention (Sydney Health Literacy Lab (SHeLL) Health Literacy Editor) and control (usual processes)

[figure not shown]

**Figure 1.** Survey flow

## Intervention groups

**Intervention (SHeLL Health Literacy Editor):** Participants will have access to the Editor (<https://shell.techlab.works/>) and self-directed training materials. The Editor is an online browser-based tool that helps users develop text-based health education materials that adhere to health literacy guidelines. The Editor comprises six assessments: readability, complex language, passive voice, text structure, lexical density and diversity, and person-centred language. These are each presented as global scores, with additional, more specific feedback flagged in the text itself. Several training resources embedded within the intervention include:

- Help page:** The Editor's help page containing instructions, video tutorials and worked examples
- Self-check tool:** 5 questions to check understanding of key concepts (available from the help page)
- Quick start guide:** A 2-page PDF introducing key concepts (available from the help page)

Participants in this group will also be invited to take part in a 30-minute Zoom call. Participants will be introduced to the tool and any relevant training resources, with opportunity to ask questions. If participants are not able to make the Zoom meeting they will have access to a recording of the same content. Zoom attendance and viewing of the recorded training will be monitored for adherence.

[figure not shown]

**Figure 2.** Screenshot of the SHeLL Health Literacy Editor.

**Control:** Participants will be asked to use their usual processes to revise the text. No training is provided prior to the task revision task. Participants will have the option to take part in SHeLL Health Literacy Editor training *after* completing the revision task (i.e. after completing their participation in the trial).

### *Participants and recruitment*

**Participants:** Eligible participants are Australian people whose work or study involves developing health information. This can include, for example, health information providers, health services staff, and clinicians. Students in medicine, allied health and health sciences are also eligible to take part. Participants are not eligible to take part if they have previous experience using the Health Literacy Editor.

Participants will be recruited through the investigators' existing networks such as the Health Literacy Hub network which comprises >1000 members across Australia. Information about the study will be circulated via communication platforms such as newsletters and social media.

Participants who complete the text revision task will be provided with a \$50 gift card. Participants who take part in the focus groups will receive an additional \$50 gift card.

**Consent:** Participants will be given the participant information statement and can indicate their consent using an online survey (Qualtrics platform). All participants will be asked to provide an email address or phone number by which study researchers may contact them with invitations to the training components, the text revision task and if selected, the interviews. This email address will also be used to remind participants to complete the revision task (see below for more detail). At the end of the trial task, participants in the Health Literacy Editor group can also indicate their consent to take part in the online focus-groups.

98  
99

## Procedure

100 **Survey 1:** Following the consent process, the survey will ask for demographic and  
101 professional information (approx. time 5 minutes).

102 Participants will then be randomised to intervention group. Participants allocated to use the  
103 intervention will complete training via Zoom (see above, 30 minutes).

104 **Survey 2 (revision task and process evaluation):** Participants will then be asked to revise  
105 3 texts (total approx. 600 words, example texts are provided in the attachment 'survey for  
106 health information providers.' Texts may be adjusted after piloting to ensure the task is  
107 manageable for participants). Participants will be provided with instructions to revise the text  
108 so that it is easier to understand. To aid revision, a brief description of the target audience  
109 and purpose for each text is also provided. Estimated time to complete the task is 40  
110 minutes. After revising the texts, participants will be asked to complete survey items about  
111 self-reported estimates of time taken to revise the text, usability, acceptability, and  
112 engagement/fidelity.

113 **Reminder emails:** If the revision task is not completed, two reminders will be sent, at 1  
114 week and 2 weeks following from training (intervention group) or consent (control group).

115 After completion of survey 2, participants will be emailed a \$50 gift card to thank them for  
116 their time completing the trial.

117

## Measures

118 **Primary outcome:** Grade readings score (Simple Measure of Gobbledygook). The Editor  
119 uses the SMOG readability formula [8], which is considered a more reliable, robust, and  
120 conservative estimate of grade reading score compared to other readability formulas [9-11].  
121 The Editor's automated SMOG scores are more accurate than those of other online SMOG  
122 calculators [12]. In Australia, health literacy guidelines recommend that information is written  
123 at a grade 8 reading level or lower [13].  
124

125

## Secondary outcomes:

- 127 1) **Text accuracy / retention of meaning:** Two researchers will assess each text for  
128 retention of key messages (determined a-priori), and identify any additional or  
129 incorrect information.
- 130 2) **Text Complexity:** The Editor's text complexity score reports the proportion (as a %)  
131 of words in the text being assessed that are flagged by the program as 'complex.'  
132 This includes acronyms, any words for which a simpler alternative has been  
133 identified, based on public health and medical thesauruses, and any words that are  
134 flagged as 'uncommon' in English, according to a database of more than 270 million  
135 words.
- 136 3) **Passive voice:** The Editor's passive voice score indicates the number of passive  
137 voice in the text.
- 138 4) **Expert PEMAT assessment:** Two co-investigators will assess each revised text,  
139 masked to intervention group. Relevant PEMAT items are shown in the table below A  
140 third item, retained meaning, was also added.  
141

|            |
|------------|
| PEMAT Item |
|------------|

|                                                                |
|----------------------------------------------------------------|
| Content                                                 |
| Makes its purpose completely evident                           |
| No distracting information or content                          |
| Word Choice and Style                                   |
| Common, everyday language                                      |
| Medical terms are defined and used only to familiarise readers |
| Active voice                                                   |

- 5) **Consumer assessments of information quality: see Part 2 below**
- 6) Self-reported time to complete the task

### *Process evaluation*

Participants allocated to the intervention (Health Literacy Editor) group will be asked to complete survey items on:

- 1) **Usability:** assessed by the System Usability Scale [15, 16], and The System Usability Scale produces a score from 0 (low) to 100 (high). A score of 70 is considered 'passable,' and a score of 90 or more is considered indicative of a 'truly superior product' [16].
- 2) **Acceptability:** the Technology Acceptance Model (comprises two subscales: perceived usefulness and perceived ease of use) [17]. Each subscale produces a score ranging from 1 (low) to 7 (high). Scores are predictive of current and future use of a product [17].
- 3) **Engagement and fidelity:** Self-reported Health Literacy Editor training resources accessed and features within the tool used when revising the text

Participants in both conditions will be asked to briefly describe any other tools they used to revise the text e.g. Microsoft Word, Thesaurus.com.

**Focus groups:** A subset of participants in the intervention arm (n=25) will be invited to take part in focus groups to provide further feedback on the Editor and to help identify potential implementation issues. Participants randomised to the Health Literacy Editor can indicate their interest in the focus groups after submitting their revised texts. Participants invited to the focus groups will be contacted via their nominated phone number or email address (see attachment), with one reminder phone call and email provided if needed.

Semi-structured focus group questions will elicit detailed data about components shown in Box 1. We anticipate 4 groups of 4-8 participants each (total approx 20-30 participants) to elicit sufficiently rich data. We will purposively sample participants to ensure there is a range of people with different characteristics e.g. gender, age, experience in varying sectors/professions and varying confidence in producing plain language written health materials.

#### **Box 1. Topic guide for semi-structured focus groups**

1. General impressions/feedback on the Health

|                                                                                       |
|---------------------------------------------------------------------------------------|
| Literacy Editor                                                                       |
| 2. Discussion of training resources                                                   |
| 3. Reflections on the revision task, including aspects that were easy and challenging |
| 4. Incorporating the Health Literacy Editor into workflows and business as usual      |
| 5. Potential barriers and facilitators to embedding the Editor into workflow          |

174 After completion of the focus groups participants will be emailed a gift voucher (\$50).

## 175 *Analysis*

176

177 **Sample size:** Sample size estimate of 120 (60 participants per group) is based on 90%  
 178 power at  $\alpha = 0.05$  to detect a moderate effect size (Cohen's  $f = 0.30$ ) in the main outcome  
 179 (grade reading score). An additional buffer (total 144) will allow for 20% drop-out before the  
 180 text revision task is completed.

181 **Statistical analysis:** Univariable regression models will be performed to analyse differences  
 182 in information quality for resources developed using the Health Literacy Editor (intervention)  
 183 and control (Grade Reading Score as primary outcome). Participants in the control group  
 184 who state that they have used the Health Literacy Editor to revise the texts will be excluded  
 185 from the analysis.

186 Descriptive statistics will be used to analyse usability, acceptability and fidelity (intervention  
 187 group only).

188 **Qualitative analysis:** Focus-groups will be audio-recorded and transcribed, then analysed  
 189 using thematic analysis. We anticipate a sample size of approximately 25-30, as this is a  
 190 typical number included for qualitative research.

191

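### The primary model is fixed as arm-only although professional data are collected before randomisation; a short pre-named covariate list could add precision at almost no cost

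*Protocol*

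**What the plan says.** In Part 1, under Analysis, the statistical analysis paragraph reads "Univariable regression models will be performed to analyse differences" in information quality between the Editor and control groups, with grade reading score as the primary outcome. It names no covariate. The outcome is defined under Measures as "Grade readings score (Simple Measure of Gobbledygook"), a continuous score.

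The Procedure section sets the order of events. "Following the consent process, the survey will ask for demographic and" professional information, and only after that: "Participants will then be randomised to intervention group".

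The Participants and recruitment section defines a broad population. On the working side, "This can include, for example, health information providers, health services staff, and clinicians". In addition, "Students in medicine, allied health and health sciences are also eligible to take part".

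The sample size paragraph reads "Sample size estimate of 120 (60 participants per group) is based on 90"% power at α = 0.05 for Cohen's f = 0.30, which is an unadjusted two-group effect.

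**The concern.** Each participant produces the outcome by rewriting text, so professional background could plausibly predict the SMOG grade reached. The variables that describe it are recorded before allocation, so adjusting for them cannot introduce post-randomisation bias. In a linear model, adjusting for a prognostic baseline variable shrinks the residual variance and hence the standard error of the arm effect. The protocol does not leave this open: it names an arm-only model, and an analysis plan that adjusted would depart from it. At stake is the precision of the primary estimate, not its validity.

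**Working it through.** **Inputs from the protocol (Part 1, Analysis).** Total N = 120, 60 per arm; α = 0.05, taken as two-sided because that reproduces the stated N; Cohen's f = 0.30; target power 90%.

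**Inputs assumed.** R² is the share of within-arm SMOG variance explained by the Survey 1 variables. The protocol gives neither this nor an SD for SMOG, so R² is varied from 0 to 0.30. The covariates are taken to use 4 degrees of freedom.

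**Step 1: reproduce the plan's figure.** For two equal arms d = 2f = 2 × 0.30 = 0.60. The normal approximation gives 59 per arm, or 118 in total. For the exact calculation, use a noncentral F with 1 and N − 2 degrees of freedom and noncentrality λ = N × f².
- N = 118: λ = 118 × 0.09 = 10.62, power 89.8%.
- N = 119: λ = 10.71, power 90.1%.
- N = 120: λ = 10.80, power 90.3%.

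The smallest adequate N is 119, hence 120 with equal arms. The plan's figure reproduces and agrees with its univariable model. A one-sided test would need only 48 per arm, or 96, which does not match.

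**Step 2: add covariates.** The noncentrality becomes λ = N × f² / (1 − R²), the denominator degrees of freedom become 120 − 2 − 4 = 114, and the standard error is multiplied by √(1 − R²).

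| Assumed R² | λ at N = 120 | SE multiplier | Power at N = 120 | Even N for 90% power |
|---|---|---|---|---|
| 0 | 10.80 | 1.000 | 90.3% | 120 |
| 0.05 | 11.37 | 0.975 | 91.7% | 114 |
| 0.10 | 12.00 | 0.949 | 93.0% | 108 |
| 0.20 | 13.50 | 0.894 | 95.4% | 96 |
| 0.30 | 15.43 | 0.837 | 97.4% | 84 |

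**Step 3: the cost if the covariates are useless.** The R² = 0 row is the worst case. Four degrees of freedom are spent for nothing, yet power is 90.3%, the same to one decimal as without adjustment. With ten useless covariate degrees of freedom it is still 90.3%.

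**Step 4: the gain.** Against 90.3% unadjusted, the gain in percentage points is 91.7 − 90.3 = 1.4 at R² = 0.05, 93.0 − 90.3 = 2.7 at 0.10, and 95.4 − 90.3 = 5.1 at 0.20.

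**The case against.** The strongest reply is that nothing here is an error. With two randomised arms, the univariable comparison is valid and unbiased, and it matches the sample-size basis and meets the 90% target. That stands in full.

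The second reply is that the gain is hypothetical. The protocol reports no link between writer characteristics and SMOG grade. Broad eligibility does not show that the grades of the revised texts differ by role, since everyone is asked to revise three supplied texts. The most useful covariate, a score for each participant's own writing before randomisation, does not exist because no such task is described. This also stands, and it is why R² = 0 and 0.05 belong in the table. It does not remove the point, because the cost in the worst case is negligible.

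Three stronger readings are tempting, and the protocol does not support them.
- A reader might infer that chance imbalance in experience biases the unadjusted estimate. It does not: under randomisation such imbalance is part of the sampling variability that the standard error already covers. Adjustment reduces that component only so far as the covariates are prognostic.
- A reader might infer that randomisation is unstratified. The Procedure section gives no method either way.
- A reader might infer that confidence in plain-language writing is already available as a baseline covariate. The protocol mentions it only as a characteristic for choosing focus-group members and does not say that it is recorded before randomisation. Only demographic and professional data are confirmed at that point.

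The size of the drop-out buffer is a separate matter and lends no weight here.

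**Conclusion.** The point holds as an efficiency recommendation of modest weight. The protocol commits to an arm-only primary model while holding pre-randomisation variables that might predict the outcome, and so forgoes whatever precision they offer. At the planned 120 participants, the benefit of adjusting runs from nothing at R² = 0 to about 5 points of power at R² = 0.20, with standard errors up to 11% smaller (1 − 0.894 = 0.106). These figures rest on an assumed R², four covariate degrees of freedom, a two-sided 5% test and the plan's own f = 0.30. It would go too far to say that meaningful precision is demonstrably lost or that the planned analysis is flawed.

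**What to change.** In Part 1, Analysis, change the primary model to a linear regression of SMOG grade on arm plus a short list of Survey 1 variables, fixed before any outcome data are seen. The list should contain professional role (student; clinician or health services staff; health information provider). Plain-language experience or confidence should be added only if Survey 1 records it before randomisation, which needs checking against the survey itself. Report the unadjusted model as a supporting analysis.

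The sample size can stay as it is. For professional role the change is one of wording, since professional data are already to be collected. The statistical cost is a few degrees of freedom, and the gain may prove small because the covariates are only proxies for writing skill.

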## 192 *Part 2: Consumer assessments of revised materials*

### 193 *Study design*

194 This component will provide the secondary outcome measure for part 1 (the consumer  
 195 assessment of revised texts). Data will be collected via survey.

### 196 *Participants and recruitment*

197 A subsample of the revised texts will be assessed by two consumers requiring a total 150  
 198 consumers. Participants will be recruited via community events and on-site at TAFE NSW  
 199 venues. Members of the study team will explain the study and the health topics that  
 200 participants will be asked to read about. Interested participants will then be directed to the  
 201 landing page of an online survey where they can read the PIS and give informed consent  
 202 before participating in the study. To be eligible, participants must be adults (18 years and  
 203 over) with less than a university level of education, or may have a university level of  
 204 education if this was obtained overseas and English is not their main language. Each  
 205 participant will receive a \$25 gift voucher to thank them for their time.

## Survey

A Qualtrics survey will collect demographic data on e.g. age, gender, education, cultural diversity and health literacy (see survey attachment).

Each consumer will assess two sets of paired texts (one original text, one revised by a single participant from part 1). This assessment will be completed using selected adapted items from the 'information and presentation' subscale of the e-Health Impact Questionnaire -Part 2[14]. This comprises 4 statements, and consumers are asked to select which version of the text better reflects the statement. Consumers will also rate the texts according to two additional items asking which text " more clearly helps you know what to do next" and "would you be more likely to share with family and friends." (See survey attachment). Participants will receive a paper copy of these texts so that they are easier to compare side by side (see example of side-by-side text comparison), and can add comments to the paper copies to show which sections of the document are difficult to understand.

We expect it will take participants 15 minutes to complete the study.

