## Analysis

See analysis section for Part 1. This data will be used as a secondary outcome measure for the trial analyses.

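### Part 2 produces crossed repeated ratings (two per consumer, two per revised text), but the protocol sends them to the Part 1 univariable regression on arm and leaves the arm of a consumer's two pairs open

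*Protocol*

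**What the plan says.** Three statements in Part 2 of the protocol fix the structure of the consumer data.

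- Participants and recruitment: "A subsample of the revised texts will be assessed by two consumers requiring a total 150" consumers.
- Survey: "Each consumer will assess two sets of paired texts (one original text, one revised by a single participant from part 1". For each item the consumer picks the original or the revised version.
- Analysis: "See analysis section for Part 1. This data will be used as a secondary outcome measure for the trial analyses".

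The Part 1 Analysis section plans univariable regressions comparing intervention with control. It names no term for consumer, text, writer or topic. Under Procedure, each Part 1 participant revises three texts. No rule is given for which revised texts enter the subsample, or for the arm of a consumer's two pairs.

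**The concern.** Two choices by the same consumer are likely to be alike, because some readers tend to prefer the revised or simpler version whoever wrote it. Two choices about the same revised text are likely to be alike because they concern the same piece of writing. Texts by one writer share that writer's skill. A univariable regression on pair ratings ignores all three links.

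The effect of the consumer link depends on how pairs are handed out. If both of a consumer's pairs come from one arm, differences between consumers add to the noise in the arm contrast. If there is one from each arm, they cancel. The wording about a single participant can mean that both pairs come from one writer, and so one arm, or only that each revised text has one author.

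The aim of the trial is text that is easier to understand. The reading grade, complexity and passive-voice scores come from the Editor itself, and retention of meaning and PEMAT are rated by the research team. Part 2 is the only judgement by lay readers, so its standard errors should be right.

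**Working it through.** **Counts, from the protocol**

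- Pair assessments: 150 consumers × 2 pairs = 300.
- Revised texts at two consumers each: 300 / 2 = 150.
- Pool of revised texts: 120 × 3 = 360 to 144 × 3 = 432, so the subsample is 35–42% of it.
- Writers: at most 144. Since 150 exceeds 144, some writers must contribute more than one text.

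The 150 consumers have no power calculation to reproduce. The only powered figure is the Part 1 total of 120, and it does reproduce: a two-group F test with f = 0.30, 5% alpha and 90% power needs 118.7, and power at 120 is 0.903. This point does not touch it.

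**Assumptions, not in the documents**

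Let rc be the correlation between two ratings by one consumer, and rt the correlation between two ratings of one text. Each is varied from 0.1 to 0.3. Total variance is 1, the response is treated as continuous, and there is one response per pair. No separate writer level is modelled.

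**Formulas**

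The univariable model takes the variance of the arm contrast as 1/150 + 1/150 = 0.0133, a standard error of 0.115. The true variance is this times a design effect (DEFF):

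- both of a consumer's pairs from one arm: DEFF = 1 + rc + rt
- arm random per pair: DEFF ≈ 1 + rt
- one pair per arm: DEFF = 1 − rc + rt

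The true type I error of the nominal 5% test is 2 × [1 − Φ(1.96 / √DEFF)].

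**Results for rc and rt each 0.1 to 0.3**

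| Assignment | DEFF | True type I error |
|---|---|---|
| Both pairs from one arm | 1.20 to 1.60 | 7.4% to 12.1% |
| Arm random per pair | 1.10 to 1.30 | 6.2% to 8.6% |
| One pair per arm | 0.80 to 1.20 | 2.8% to 7.4% |

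**Check by simulation** (6,000 runs per setting, 150 consumers, 150 texts; rc = 0.3, rt = 0.2)

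| Assignment | Type I error | SD of arm estimate | Mean arm estimate |
|---|---|---|---|
| Both pairs from one arm | 11.0% | 0.143 | 0.001 |
| Arm random per pair | 7.7% | 0.127 | −0.001 |
| One pair per arm | 4.0% | 0.110 | −0.001 |

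The true effect was zero, so none of the three schemes biases the estimate.

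**Gain from one pair per arm**

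- Against random assignment: 1 − 1.0/1.2 = 17% less variance at rc = rt = 0.2, and 1 − 1.0/1.3 = 23% at 0.3.
- Against both pairs from one arm: 1 − 1.0/1.4 = 29% at 0.2, and 1 − 1.0/1.6 = 38% at 0.3.

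**Balance alone is not enough**

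With one pair per arm, the univariable test is exact only when rc = rt. At rc = 0.1, rt = 0.3 its type I error is 7.4%. At rc = 0.5, rt = 0.2, outside the main range, it is 1.9%.

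**The case against.** **Silence on assignment.** The protocol does not say that pairs are unbalanced by arm, and pack allocation and clustering terms are often left to a statistical analysis plan or manual that is not shown here. A reader might infer that both pairs do come from one arm. The wording permits that but does not state it, and the counts do not settle it: 75 writers × 2 texts gives 150 texts, but so do other layouts. This part of the objection stands. However, the protocol does not leave the analysis open, since it expressly assigns the Part 1 method. Pack allocation must also be settled before paper copies are given out, because no later model recovers a within-consumer contrast that was not collected.

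**Bias.** A reader might infer that consumer and text differences bias the arm effect. With random assignment they add noise only. Bias would need non-random assignment, for example by site or topic, which the documents neither state nor rule out.

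**Direction.** A reader might infer that the p-value must be too small. It is too small under the first two schemes. With one pair per arm it can be too small or too large. Under random assignment the inflation comes from text correlation, not consumer correlation.

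**Unit of analysis.** The Part 1 sample size counts writers, "Sample size estimate of 120 (60 participants per group) is based on 90" per cent power, although each revises three texts. The Part 2 data could likewise be reduced to one value per writer. If each consumer also rated only one writer, those values would be independent and the inflation would not arise. This is possible but not stated, and consumer correlation would remain wherever one consumer rates two writers.

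**Approximation.** The response is a choice between two versions, not a continuous score. A within-pair choice removes a consumer's general rating level and leaves only a tendency to prefer revised versions, so the assumed consumer correlation may be too high. This stands as a limit on the figures.

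**Conclusion.** The point holds in a limited form. The protocol specifies crossed repeated ratings and refers them to a model without any term for the repetition. Run on pair ratings, that model gives wrong standard errors. Over assumed correlations of 0.1 to 0.3, the true type I error is about 6–9% with random assignment, about 7–12% if both of a consumer's pairs share an arm, and about 3–7% with one pair per arm. The first range is the fair one to quote if assignment is random; the second applies only on one reading of ambiguous wording.

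The figures rest on assumed correlations, a continuous approximation, and analysis at the level of the pair. The documents support neither a claim that the allocation is unbalanced nor a claim that the arm estimate is biased. Only a secondary outcome is affected; the primary outcome and its sample size are not.

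**What to change.** - **Part 2, Survey:** state that each consumer receives one pair with an intervention-revised text and one with a control-revised text, in random order. Reword the phrase about a single participant so that it has one meaning.
- **Part 2, Participants and recruitment:** state that the subsample is drawn at random, stratified by arm and source text.
- **Part 2, Analysis:** replace the cross-reference with a model for the binary choice, with fixed effects for arm and source text, that accounts for clustering by consumer and by Part 1 writer. Crossed random effects or two-way cluster-robust errors would do. This is needed even with balanced allocation.

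The cost is a revised allocation list for the paper packs and a somewhat more complex model. The numbers of consumers, texts and vouchers do not change.
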